### Randomization

Participants will be randomly assigned to a control (DeCM as routine care) or treatment (DeCM + supported ACD) arm. Randomization will be stratified by gender and study arm. Because previous research indicated increased dropout rates in the supported ACD condition [9], stratified randomization by study arm will be conducted in a 2:1 (treatment:control) ratio, which is expected to result in approximately balanced groups of complete data in the two studyarms. During data collection, the ratio will be monitored and adjusted as needed to ensure balanced groups by the end of the study.

The allocations will be computer-generated using *R* package blockrand [13] with a block size of 9 for studyarm allocation. Separate randomization lists will be kept by gender as well as for each dementia care manager to ensure balanced recruitment ratios across individuals.

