**Fig. 2 Fig2:**
[figure not shown]
Design and scheduled appointments, assessments and interventions of the DECIDE-2 study

In the first and the last DeCM consultation appointment (T1 and T2), participants in both study arms will answer relevant study questions containing the pre-post assessment of primary and secondary endpoints, as well as the assessment of DeCM (not part of the study, see Material section). The last DeCM consultation (T2) will be scheduled six months after T1 ($$\pm$$ 30 days). Participating proxies in the treatment arm will answer additional questions included in T1 (as $$\text {T1}_{Treatment}$$) concerning treatment preferences of the PwD. If an advance directive is present for participating PwD in the treatment arm at T2, their proxies will complete additional study questions in T2 concerning the PwD’s treatment preferences ($$\text {T2}_{Treatment}$$). In both of these cases, the participating PwD will be absent during this query, as this could influence the ACD process and relevant endpoints.

Between T1 and T2, participants in the treatment arm will complete two supported ACD appointments. The time window between baseline assessment (T1) and the first ACD appointment (ACD1) will be 1-30 days, and the time window between the two ACD appointments (ACD1 and ACD2) will be 1-15 days. In the first appointment (ACD1), participants will complete the value anamnesis as the first part of supported ACD with their proxy present. If required, it is possible to split the completion of the value anamnesis into several appointments to reduce stress for PwD. In the second ACD appointment (ACD2), participants in the treatment arm and their proxy will finalize the process of supported ACD, deciding on their preferred form of advance health care planning and receiving support in its implementation. If they choose an advance directive or a guardianship directive, the dementia care manager will assist in drafting the document. If they opt for a power of attorney, they will be advised to consult a notary or counselling centre for PwD. If they decide against any form of advance directive, this decision will be documented. In the case of a decision to create an advance directive, a standardized assessment of participants’ capacity to consent will be conducted. A document with the participants’ decision regarding their own advance healthcare planning will be handed over to individual participants and their proxies for further use.

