### Outcome measures

The primary and secondary endpoints were chosen based on DeCM [39, 40] and advance care planning trials [4, 5]. The primary endpoints are the prevalence and validity of advance healthcare planning documents (advance directives or others) and proxy burden at pre- vs. post-measurement. Secondary endpoints are decisional conflict, patient autonomy, and patient-proxy congruence in preference. Details about the measurement of endpoints are provided in Material section.

Furthermore, the following demographic and clinical variables will be recorded: age, gender, education level, psychiatric comorbidities, health literacy, and the need for autonomy in medical decision-making. Although only age has previously been shown to be associated with the primary endpoints [41], the additional variables will be collected to provide a comprehensive description of the study population and to enable exploratory analyses.

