#### Statistical analyses

Assessment of the prevalence and validity of advance directives will be based on Bayesian generalized linear mixed-effects models. Bayesian estimation is more appropriate than maximum likelihood for smaller sample sizes, when the priors are chosen carefully [44]. We will use probit models modeling the change in the probability of the presence and validity of advance directives over time given the experimental condition and possible covariates (see Outcome measures section).

Outcome variables in these models are a) the binary variable for presence of an advance directive (yes/no), and b) the binary variable for the validity of the advance directive in the sense that it was both voluntarily given and based on informed consent (yes/no). In these models, the condition-by-time interaction and the contrast (whether the pre-post change in the ACD + DeCM condition is more pronounced than in the DeCM condition) are of primary interest. Likewise, analyses of proxy burden and of secondary endpoints will be based on Bayesian linear mixed effects models. Scale scores based on 5-point Likert scale items usually justify the use of ‘normal’ linear mixed effects models. If this is not feasible, the outcomes will be modeled as (ordered) categorical. To avoid loss of sample size, and consequently loss of statistical power, missing data in all model variables will be multiply imputed where appropriate (see Exploratory statistical solution development for missing data and small sample sizes section).

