### Quality control

For quality assurance and control, all study personnel will receive training in content-related, methodological, ethical, legal, and organizational aspects [53]. All dementia care managers have undergone comprehensive ACD-training provided by experts, equipping them with specific knowledge and skills required to conduct supported ACD with the target population. A small pilot study ($$n < 5$$) will be conducted and evaluated prior to the main study so that any required modifications can be incorporated into the manual of operations. Necessary changes to established procedures will be justified, documented and communicated to all study personnel in a timely manner. Any amendment will be submitted to the responsible ethics committee.

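### Randomisation lists are kept by gender and dementia care manager, but the models as described commit to neither factor and manager is not on the covariate list they point to

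*Protocol article*

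**What the plan says.** The Randomization section opens with "Randomization will be stratified by gender and study arm", gives a 2:1 treatment-to-control ratio "with a block size of 9 for studyarm allocation", and ends with "Separate randomization lists will be kept by gender as well as for each dementia care manager to ensure balanced recruitment ratios across individuals". Manager is therefore a stratification factor in practice, although the opening sentence does not name it. Blocks of 9 at 2:1 within a manager's list mean that each manager is expected to serve both arms. Quality control fits that reading: "All dementia care managers have undergone comprehensive ACD-training provided by experts".

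Managers are also close to the outcome. Under Procedure, Data collection, when a participant chooses an advance or guardianship directive, "the dementia care manager will assist in drafting the document". Under Data management, managers carry out the data collection.

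Statistical analyses describes Bayesian (generalized) linear mixed models of change over time, "given the experimental condition and possible covariates (see Outcome measures section". The section it points to says "the following demographic and clinical variables will be recorded: age, gender, education level, psychiatric comorbidities, health literacy", and adds need for autonomy. It remarks that only age has been linked to the primary endpoints and that the other variables serve description and exploratory work. Manager is not on that list, nor among the moderators, mediators and confounders in Table 1. No random effects are stated.

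**The concern.** A factor used to build the randomisation lists normally belongs in the primary model, so that the standard errors match the way participants were allocated. Here the model's covariates are given by cross-reference to a list of participant variables. One stratification factor is not on the list. The other is there only as something that may be used.

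Two things could follow. If managers differ in how much their participants change, whichever arm those are in, an analysis without manager leaves that variation in the residual and gives up precision that the stratified lists made available. If managers differ in how well supported ACD works in their hands, an analysis that ignores this treats the effect as better known than it is for managers in general. The second matters because the abstract's Discussion foresees adding supported ACD to the Dementia Care Management curriculum, where other managers would deliver it.

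**Working it through.** **Step 1: the texts side by side.**

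| Factor | Randomisation lists | Outcome measures list | Committed as a model term |
|---|---|---|---|
| Gender | yes | yes | no |
| Dementia care manager | yes | no | no |

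**Step 2: the plan's own figure.** Required sample size and power analysis gives about 150 participants for power above .8 at a moderate effect. Alpha, SD, variance components and numeric dropout are not given, so the simulation cannot be rebuilt exactly. Assume two-sided alpha 0.05 and d = 0.5, with power = Φ(d·√(n₁n₂/(n₁+n₂)) − 1.96):
- 100:50: 0.5 × √33.33 − 1.96 = 0.927, power 0.823.
- 75:75: 0.5 × √37.5 − 1.96 = 1.102, power 0.865.

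The stated figure is compatible with this, with little to spare at 100:50.

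**Step 3: where manager enters the pre-post contrast.** For participant i of manager j, write the change from T1 to T2 as D = c_j + (δ + b_j)·arm + e. Stable differences in level between managers have already been subtracted out. What remains is c_j (a manager's shift in change, shared by both arms; its share of the change variance is written ICC) and b_j (manager variation in the effect, variance τ²). Total change variance without b_j is set to 1.

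**Step 4: shared shift only (τ² = 0).** With 2:1 allocation within manager, c_j cancels from the arm difference but stays in the residual if manager is omitted. The true variance is (1 − ICC)(1/n_T + 1/n_C), and the model without manager reports roughly 1/n_T + 1/n_C. The SE is therefore too large by about 1/√(1 − ICC): 1.010 at ICC 0.02 and 1.054 at 0.10.

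A simulation checked this (N = 150, about 2:1 within manager, 20,000 runs per setting; assumed 3, 5 or 8 managers and ICC 0.02, 0.05 or 0.10). Under no effect, mean reported SE over actual SD ran from about 1.00 (0.1714/0.1720; 3 managers, ICC 0.02) to 1.06 (0.1712/0.1617; 5 managers, ICC 0.10). Type I error without manager was 0.037 to 0.051. Power at d = 0.5:

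| Managers | ICC | Manager omitted | Manager fitted | Loss (points) |
|---|---|---|---|---|
| 3 | 0.02 | 0.818 | 0.822 | 0.4 (smallest) |
| 5 | 0.10 | 0.837 | 0.858 | 2.1 |
| 8 | 0.10 | 0.824 | 0.847 | 2.4 (largest) |

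**Step 5: effect varying by manager (τ² > 0).** The variance becomes (1 − ICC)(1/n_T + 1/n_C) + τ²/M for M managers. With M = 5, ICC 0.05, τ² = 0.05 and 100:50, this is 0.95 × 0.03 + 0.05/5 = 0.0385, so the SE is 0.196 (simulated 0.197). The analysis without manager reports 0.1745. Over 3 to 8 managers and τ² from 0.02 to 0.10, all assumed, type I error was 0.054 to 0.167 with manager omitted. With manager fitted but the effect held common, it was 0.059 to 0.181. Fitting manager alone does not deal with this case. The figures illustrate the mechanism and do not estimate anything in this trial.

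**Step 6: what this means for the model.** A manager term in the change-score analysis corresponds to manager-by-time in the longitudinal model. A plain manager intercept there absorbs level differences only, so it addresses neither Step 4 nor Step 5. The simulation uses a continuous change score and is only a guide for the probit models.

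**The case against.** The strongest reply is that the article is silent and does not exclude manager. It names mixed models without stating any random effect, not even one for participant. Manager would naturally sit there, and the statistical analysis plan is not shown. This stands as a limit: a reader might infer that manager is in no model, but the document supports only that manager is in none of the model descriptions it gives. It does not remove the point, because the article does name where its covariates come from, and a factor used for the lists is missing there.

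A reader might also infer that every primary interval is wrong, or that all are too narrow. The document does not support that. With little manager variation the error is close to nil. With a shared shift it is conservative. Intervals are too narrow only if the effect differs between managers, which nothing in the article shows. Common training, supervision and case conferences are meant to keep delivery uniform, and for a power of attorney participants are referred elsewhere. Whether such variation belongs in the interval also depends on whether inference is to these managers or to managers at large.

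Finally, a reader might take the usual inflation for an omitted stratum in a T2-only comparison (3 to 5% if managers explain 5 to 10% of T2 variance). The trial plans a condition-by-time contrast, in which stable level differences cancel in the linear case, so that figure does not apply.

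**Conclusion.** The point holds in a limited form. As described, the analysis does not carry the factors that the randomisation lists use: manager is absent, and gender is available but not committed. If managers differ in change equally in both arms, the price is a standard error about 0 to 6% too large and about 0.4 to 2.4 points of power at d = 0.5. These figures rest on assumed values (3 to 8 managers, 2 to 10% of change variance, N = 150 at about 2:1, two-sided alpha 0.05). If the ACD effect varies by manager, intervals that ignore it are too narrow for inference beyond these managers. The size of that cannot be fixed, because neither the number of managers nor any variance is given. The loss is modest, and the correction is cheap enough to be worth making.

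**What to change.** - In Statistical analyses, commit gender and dementia care manager, each with its time interaction, as terms in all primary models. Manager can be fixed strata or a random effect with a weakly informative prior; say which.
- Add a planned sensitivity analysis in which the condition-by-time effect varies by manager. Note that with few managers this variance will depend heavily on its prior, so state the prior.
- State the number of managers.
- In Randomization, reconcile the opening sentence, which names study arm as a stratifier and leaves out manager, with the per-manager lists in the closing one.

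The cost is a few sentences. Gender and manager are already known from the randomisation lists, and no further data or participants are needed.

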### Procedure

#### Data collection

The procedure of the data collection process is shown in Fig. 2. Recruited individuals fulfilling the inclusion criteria will be asked to participate in the study. In the first appointment (T0), information about the study will be given and, if individuals wish to participate, consent for participation will be collected from the PwD as well as from their proxy. All information given to individuals prior to study inclusion will be standardized over both study arms and random assignment to study arm will take place afterwards.

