#### Recruitment

Recruitment will focus on patients or clients from the dementia care network in Siegen-Wittgenstein and will be further integrated within the locally operating DeCM (the dementia care managers will approach suitable patients in their work context). Recruitment will also extend to surrounding regions of Siegen-Wittgenstein to inform general practitioners, neurologists, pharmacies, associations, self-help groups, and the general public through local media channels. The network of participating practice partners represents the necessary care areas for DeCM and PwD (initial diagnosis, sector transitions, etc.) and includes an entire region with urban and rural areas. All partners have established care structures and prior experience in conducting and participating in scientific projects [14, 15], ensuring access to the target audience relevant to this trial. DeCM was already implemented in Siegen-Wittgenstein [16], and the dementia care managers already provide DeCM. They will invite patients or clients who meet the inclusion criteria. Based on our previous projects, recruitment in the hospital setting (geropsychiatry) will be supported by the physicians of the memory clinic located in the Klinikum Siegen.

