#### Data management

##### **Data collection**

Data collection conducted by the dementia care managers will be computer-assisted using the proprietary software of the German Center for Neurodegenerative Diseases in Greifswald and will be stored on the Center’s local servers. For the subpopulation of participants who create an advance directive as part of the study, audio recordings of the approximately 20-minute interview section to assess capacity to consent (CAT-AD) will be made using dedicated digital voice recorders. These recordings will be re-evaluated by the psychotherapists from the research team to assess inter-rater reliability and to ensure quality control of the assessment.

All personnel managing personal data as part of the research project will be made aware of applicable legal requirements and potential risks. Before the start of fieldwork, those involved in data collection will be thoroughly prepared, trained and their activities will be constantly monitored. Data collection will be accompanied by continuous data monitoring and standardized reporting. Monitoring will focus on aspects like missing values, implausible values, and value distributions. The study has been registered in the German Clinical Trials Register (DRKS Trial no. DRKS00036478) and this protocol was written following the SPIRIT guidelines (see Additional file 2). External quality will be further assured through external expert advice on ethics (see Ethical considerations section).

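### The text implies that the arm is known by the T1 baseline visit, whose data unblinded care managers collect; a single fixed block size adds a lesser predictability problem

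*Protocol article*

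**What the plan says.** **Timing.** Under Procedure, Data collection, information and consent take place at T0, and "random assignment to study arm will take place afterwards". The endpoints are first measured after that: "In the first and the last DeCM consultation appointment (T1 and T2), participants in both study arms will answer relevant study questions". The same section calls T1 the baseline: "The time window between baseline assessment (T1) and the first ACD appointment (ACD1) will be 1-30 days".

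**Content of T1.** Part of the visit depends on the arm: "Participating proxies in the treatment arm will answer additional questions included in T1". These questions concern the treatment preferences of the person with dementia.

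**Who does what.** Under Recruitment, "the dementia care managers will approach suitable patients in their work context". Under Data management, "Data collection conducted by the dementia care managers will be computer-assisted". Study design, Procedure and Quality control show that the managers also conduct supported ACD. Single-blind refers to the participants. The Discussion concedes that blinding cannot be complete, because the managers belong to the research team and the additional ACD appointments are visible.

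**Allocation.** Under Randomization, the ratio is 2:1 in favour of treatment, "with a block size of 9 for studyarm allocation". The article adds: "Separate randomization lists will be kept by gender as well as for each dementia care manager". The ratio may be adjusted during the study.

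**Analysis.** Under Statistical analyses, the quantity of primary interest is the condition-by-time interaction, that is, whether pre-post change is larger with supported ACD.

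**The concern.** A baseline that enters a change score should be fixed before anyone who can affect it knows the arm. Here the text leads the other way: randomisation follows T0, the T1 visit has an arm-specific part, and the person collecting the data is not blinded. Proxy burden, patient autonomy and decisional conflict are rating scales, and document validity rests on a self-report questionnaire. All can respond to how a question is introduced, explained or assisted, especially with cognitively impaired respondents. If T1 burden were recorded somewhat higher in the treatment arm, the same amount would appear at T2 as extra relief.

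The lesser concern is entry to the trial. Managers who invite patients, and who know the earlier allocations on a list tied to them, can sometimes work out the next one. That would allow the approach to a patient to depend on the expected arm.

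Both bear on the internal validity that the Discussion attributes to the single-blind design.

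**Working it through.** **1. Order of events.** The article gives no figure to reproduce on this point, so the statements are set side by side.

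- Inclusion at T0, then randomisation (Procedure, Data collection).
- T1 is the baseline and comes after T0 (same section).
- Treatment-arm proxies answer extra items within T1 (same section). A visit whose content depends on the arm cannot be completed without knowing the arm.
- No sentence says that the common items are completed or locked before the arm is released.

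The arm is therefore known at some time during T1 at the latest, and the text leaves open that it is known before the visit starts.

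**2. How a T1 shift enters the effect.** For a linear outcome with complete data, the condition-by-time contrast is

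effect = (T2 − T1, treatment) − (T2 − T1, control).

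If knowledge of the arm adds δ to the treatment-arm T1 mean and changes nothing else, the effect changes by −δ. For illustration only, δ = 0.1 SD would be 0.1/0.5 = one fifth of a 0.5 SD effect. Both numbers are assumptions: the article says only that effects in the moderate range are targeted, and it gives no basis for any value of δ.

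**3. Predictability of a 6:3 block.** Inputs: block of 9 at 2:1, hence 6 treatment and 3 control. The observer knows the block size and all earlier allocations on the list.

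- Expected number of certain allocations at the end of the block = 6/(3+1) + 3/(6+1) = 1.500 + 0.429 = 1.929. As a share, 1.929/9 = 21.4%.
- Enumeration of all 84 orderings gives the probability of certainty at positions 4 to 9 as 0.012, 0.048, 0.119, 0.25, 0.5 and 1.0. The sum is 1.929, as above.
- Guessing the arm with more places left is right for 6.548 of 9 allocations, or 72.8%. Always guessing treatment is right for 6/9 = 66.7%.

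**4. Scaling to about 150 participants.** The number of managers is not given. I assume 2 to 8, two lists each (by gender), of equal length.

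- 5 managers: 10 lists of 15, that is, one full block plus 6 positions. 10 × (1.929 + 0.012 + 0.048 + 0.119) = 21.1 certain allocations, 14%.
- 8 managers: 16 lists of about 9. 16 × 1.929 = 30.9, or 21% of the 144 allocations in full blocks.
- Over the whole assumed range: about 21 to 31 certain allocations, 14% to 21%.

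**5. Varying the block size.** Simulated for an observer who knows the set of sizes but not their order, with sizes equally likely and the ratio kept at 2:1:

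| Block sizes | Certain | Best guess correct |
|---|---|---|
| 9 only | 20–21% | about 73% |
| 3, 6, 9 | 3–4% | 73–74% |
| 6, 9, 12 | about 2% | 71–72% |

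Blocks of 3 alone, if known, would make 2/2 + 1/3 = 1.33 of 3 allocations (44%) certain.

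**The case against.** **The article does not state that the arm is known before T1.** This is correct. The sentence on randomisation only places it after T0. Releasing the arm during T1, after the common items, is compatible with the text, and Fig. 2 is not available here. What stands is that the article makes T1 content depend on the arm and mentions no such order. If that order is intended, one sentence settles the matter.

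**A reader might take the article to admit baseline bias**, because it says that the proxy query could influence endpoints. It does not. That remark explains why the person with dementia is absent during the query, and it describes a safeguard.

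**A reader might infer that managers hold their own lists.** The article says that lists are kept for each manager, not by whom, and custody may be covered in the full protocol. Prediction does not need the list, however. A manager who delivers supported ACD learns the earlier allocations from the work itself, and the block size is published.

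**Selection is limited.** Consent precedes allocation, so only a prediction of the next arm could bias entry. Managers are one of several recruitment routes, the gain in guessing is about 6 percentage points, and mid-study changes of the ratio may break block certainty. All of this stands, and it makes predictability the lesser part.

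**Baseline influence is limited too.** Participants are blinded, proxies answer the burden scales themselves, and the article does not say that managers read out or score them. The yes/no question on whether a document exists leaves less room for influence. These points reduce the risk but do not remove it while an unblinded manager conducts the data collection.

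**Conclusion.** The concern holds as a weakness in the stated procedure, not as evidence of bias. As written, knowledge of the arm can reach the T1 measurement through an unblinded data collector, and the change-based analysis passes any resulting shift directly into the effect. How large such a shift would be cannot be derived from the article. The conclusion rests on reading the arm-specific T1 questions as requiring the arm to be known at that visit.

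Predictability is real but secondary: 21.4% of allocations are certain in a full block, about 14% to 21% overall for an assumed 2 to 8 managers, and the best-guess rate is 72.8% against 66.7%. These figures assume that the manager knows the block size and all earlier allocations on the list, and that the 2:1 ratio stays fixed.

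The change should be made because it is cheap. The trial's validity does not stand or fall with it.

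**What to change.** 1. **Lock T1 first.** State that the allocation is released to the manager only after the common T1 assessment is completed and locked. Ask the extra proxy items after release, in the treatment arm only and before ACD1. The 1–30 day window between T1 and ACD1 leaves room for this. Do not extend these items to control proxies: questions about treatment preferences could prompt planning in the control arm and dilute the contrast.
2. **Change the lists for remaining participants.** Hold them centrally and vary the block size at random, with sizes not disclosed to managers, for example 6, 9 and 12 (about 2% certain). Avoid blocks of 3: a mix of 3, 6 and 9 lowers certainty but leaves the best-guess rate at about 73%.

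**Cost.** A short amendment, which the article says goes to the ethics committee, and regenerated lists. The manager learns the arm one step later. Recruitment is planned until January 2027, so participants still to be enrolled can benefit. If T1 is already locked before release in practice, item 1 needs only a clarifying sentence.
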